***HTT* impacts brain structure and function along the entire spectrum of repeats**: Higher repeats are associated with better cognitive skill and greater brain volume in GE and GNE individuals [13,14].**Methodological challenges of modeling age and CAG separately, versus years-to-onset model (which incorporates both):** The Kids-HD study employed an accelerated longitudinal design (ALD), the gold standard for evaluating brain development in children, which combines cross-sectional and longitudinal data to model age-related changes across a broad developmental window. This model showed not only interesting findings of accelerated striatal development, where GE children reached peak striatal volume years before the GNE group, but that these trajectories were profoundly affected by CAG repeat length [15]. We also found that every CAG repeat conferred a greater advantage in general cognitive ability [14]. This effect peaked at repeats of 43 and individuals with longer CAG repeats showed trajectories that were declining in function after age 15, likely representing changes due to the degenerative phase of the disease. The age-trajectory modeling results highlighted the profound consequences *HTT* and CAG repeat-length has on neurodevelopment. These findings recapitulate the well-established negative relationship between CAG repeat length and age of motor onset and require an updated model to take both factors, and their interactions, into account. Given the influence CAG repeats and age exert on longitudinal brain development, we began modeling the data in a Years-To-Onset (YTO) fashion to evaluate the time course of the disease from development to degeneration. The YTO model predicts the age of motor onset based on the participant’s current age and CAG repeat length. Importantly, the YTO model can reveal information about disease trajectory that is obscured when plotting data by age. For example, Reasoner et al. (2022) found that cortical volumes are similar across age groups [16], while Neema et al. (2024) found evidence for higher and lower cortical volumes depending on the YTO of the individual [17]. The critical difference between approaches is that while higher age and lower YTO both predict decline in cognitive and motoric function, age-only models ignore variability in disease trajectory caused by CAG repeat length. An example of the difference between an age-only trajectory and a YTO model is as follows: An 8-year-old with a CAG repeat length of 48 and a 22-year-old with a CAG length of 43 both have 26 YTO, despite being on opposite ends of the age trajectory model. Thus, potential differences in cortical volumes could have been missed by Reasoner et al. (2022) because participants at similar ages were at different points in their disease trajectory. Additionally, when evaluating a biomarker of degeneration in Kids-HD (neurofilament light; “NfL”), we found that NfL levels are normal as far back as 40 YTO but rise around 20 YTO [18]. These findings support the notion that the YTO model can accurately characterize the developmental phase of the disease process, which occurs 20 years before the onset of motor symptoms.**The antagonistic pleiotropy theory of *HTT* and its implications for neurodevelopment:** In our most recent publication, we revealed that GE individuals from 50−20 YTO have larger cerebral volumes, more cortical surface area, and higher IQs compared to GNE subjects, but the opposite is true after 20 YTO [17]. Striatal and pallidal volumes remain comparable in volume to GNE until 20 YTO after which they dramatically decline in volume, consistent with early vulnerability of the basal nuclei. These findings challenge the traditional concept of HD as a uniquely neurodegenerative disorder and highlight the neurodevelopmental role of *mHTT.* Additionally, Kids-HD research uncovered potential early advantages of *mHTT* in GE children, such as larger brain development that supports enhanced cognitive development and reduced depression/anxiety. However, these children will indeed develop HD, highlighting the yoking of advantage with disadvantage. Our findings support the notion of antagonistic pleiotropy in HD, where the same neurodevelopmental differences that confer early advantage eventually lead to vulnerability and subsequent degeneration [19]. Collectively, they reshape our understanding of the evolutionary implications of *mHTT* and its potential role in brain development

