### Power analysis and sample size calculation

Based on our findings from the Kids-HD sample, our central hypothesis is that GE participants will demonstrate altered trajectories in general brain size and cognition across YTO. Specifically, we predicted that GE individuals will demonstrate significantly larger brain volume (primary outcome measure) and stronger cognition scores (secondary outcome measures) prior to 20 YTO and significantly smaller brain volume and weaker cognition between 20−0 YTO. Using our updated recruitment target of 1,030 assessments across 450 participants, we estimated at least 90% power to reproduce our previous findings at p = .01 (except for cortical thickness; Table 5). Note that Table 5, which shows the results of our power analysis, includes functional and structural measures, but that our power analysis is primarily based on the structural findings from Kids-HD. Assuming 40% of participants are GE (as in the previous study), we can assume at least 400 visits from 180 unique genetically affected participants. The power analysis used the Kids-HD sample from Neema et al. (2024), and was based on 136 visits from 79 gene-expanded participants. Because the mean number of visits (and hence, statistical information) per participant will be higher in ChANGE-HD, a conservative estimate of the overall increase in statistical information (i.e., log-likelihood statistics) is obtained from the ratio of unique participants, which is 2.278. If the findings from Kids-HD hold, then the expected values of the analogous F statistics (Table 5) will increase by at least 2.278-fold. Standard power calculations using these projected F statistics yield results that exceed the above-claimed minimum statistical power.

**Table 5 pone.0336088.t005:** Tests used for hypotheses and power analysis (from Neema et al., 2024).

		Kids-HD				Change-HD		
**Measures**	**N**	**ndf**	**ddf**	**F**	**p**	**Projected F**	**Projected NCP**	**Power**
General Ability Index**	136	1	87.66	13.50	<0.001	30.78	29.445	0.997
Behavior composite**	135	2	120.27	10.91	<0.001	24.87	47.343	>0.999
PANESS**	128	1	46.12	8.92	0.005	20.34	18.933	0.956
Whole brain*	117	3	62.63	7.79	<0.001	17.76	49.491	>0.999
Cerebrum	117	3	62.55	7.80	<0.001	17.78	49.557	>0.999
Cortical gray matter*	117	1	99.90	12.22	<0.001	27.86	26.593	0.995
Cortical surface area	117	1	95.22	12.17	<0.001	27.75	26.468	0.994
Cortical thickness*	117	1	54.67	2.95	0.091	6.73	5.612	0.406

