
#### Statistical analysis using YTO Models.

We will employ a YTO model, which provides a more detailed representation of disease-related changes (between 50 and 0 YTO) than an age-based analysis [15,16,18,23]. Our statistical analyses are derived from Langbehn et al. [80] and our own work [17] investigating neural and behavioral changes across YTO. This method is based primarily on data from individuals with CAG repeats between 41 and 56 [80] but extrapolation has generalized usefully to CAG repeats extending beyond this range (40, 57–70, etc.) [17]. Because individuals with between 36–39 CAG repeats represent an incomplete penetrance group, they will be excluded from the YTO analysis and will be examined separately in exploratory analyses. Individuals with >70 CAG repeats will also be excluded as they are likely to have already begun showing motor symptoms of HD and are likely classified as patients with JOHD. All hypotheses relate to either systematic group difference between GE and GNE individuals or to differences within the GE group driven by CAG expansion length and age (or years to onset as in the NfL analysis). Our analysis approach will include the following steps: 1) age and sex correction based on the data from healthy controls, 2), estimation of YTO, and 3) YTO modeling with testing for potential additional sex differences and sex by YTO interactions.

For each dependent variable, we apply statistical corrections to separate developmental effects of typical aging from those experienced by GE individuals as part of the disease trajectory. We perform this correction by modeling age and sex effects in GNE controls using a regression that includes within-subject and within-family random effects. The models incorporate both linear and potential non-linear age relationships. Nonlinearity is modeled flexibly via restricted cubic splines (“natural splines”). The degree of non-linearity (up to five degrees of freedom) is determined by choosing the model with the lowest Akaike Information Criterion (AIC), with tied AIC values (≤ 1.0) favoring the simpler model. We also test the model for sex and sex-by-age interactions, which are excluded from the final model if found to be nonsignificant. The fitted values for this model are then subtracted from the dependent value to complete the correction.

Estimation of age of motor symptom onset is calculated using the Langbehn model [80] shown below:

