$$\begin{array}{c} Age\;of\;motor\;symptom\;onset=\text{2}\text{1}.\text{5}\text{4}-(\text{9}.\text{5}\text{5}\text{6}-\text{0}.\text{1}\text{4}\text{6}*CAG) \end{array}$$

YTO is then calculated by simply subtracting participants’ ages (in years) from age of motor symptom onset. (The abbreviation YTO, now established by precedent, stands for a slight misnomer. The value is the number of years from the mean age of onset for those with the given CAG length. It is not the individual’s number of years to onset—which is unknowable—and is slightly different from the individual’s expected years to onset, given that they have reached their current age without already experiencing onset.)

A limitation of this YTO approach is that it can only approximate the relationship between true years to HD onset and the outcome measures. As noted earlier, the YTO calculations are slightly biased estimates of participants’ expected years to onset. Furthermore, a person’s true years to onset has a probability distribution around the CAG-specific average. For concave relationships, such as those we typically expect in the neurodevelopment of brain volumes, substitution of an average value for a probability distribution causes at least slight underestimation of the predicted value that would be obtained from a model based on the true (but unknowable) number of years from onset (Jensen’s inequality).

We assess the relationship between YTO and age- and sex-adjusted outcome measures in GE individuals using an additional mixed effects regression, again including random effects for repeated measures of the same participant and for similarities between participants from the same family. Similar to the GNE model described above, the potentially nonlinear influence of YTO is modeled using restricted cubic splines with degrees-of-freedom chosen by AIC. Sex and sex interactions with YTO are tested and included in the model if significant. The mixed effect models are fitted by maximum likelihood and F-test degrees of freedom are estimated using the Satterthwaite approximation. The summary of the resulting model indicates a p-value for the effect of YTO, which, if significant, indicates a statistically meaningful difference of GE from GNE along the YTO trajectory. Finally, we plot these relationships and their 95% confidence intervals to determine where these differences occur along the trajectory (50−0 YTO)

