Like other HD studies, the ultimate goal of the ChANGE-HD study is to guide the design of interventions to prevent or mitigate HD symptoms. Reproducing the findings of early-life advantages in GE individuals observed in the Kids-HD sample [17] would bolster support for the antagonistic pleiotropy theory of HD and caution against mutant Huntington downregulation early in the disease process. Indeed, if the gene confers a benefit, then such treatments may come at a cost before neurodegeneration has begun. We also expect that studying the disease before brain function decline will reveal new neuroimaging patterns that predict neurodegeneration. For example, outlining the time course of motor and frontal resting state functional connectivity patterns may reveal when corticostriatal hypertransmission begins to negatively affect behavior. Pharmaceuticals to alter glutamatergic concentrations associated with these connectivity patterns may be a promising line for therapeutics. Finally, we will investigate how genetic modifiers (i.e., *FAN1*, *MLH1*, *PMS1*, etc.) affect the trajectory of the disease process before neurodegeneration begins. While these modifiers are related to the continued expansion of CAG repeats (somatic expansion) and well-studied later in the disease process, it is unclear how they contribute to neurodevelopment. Linking these modifiers to neurodevelopment may reveal important neuropathological insights or uncover new interventional targets.

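### The years-to-onset p-value shows change across YTO among gene-expanded participants, not the sign or place of a difference from controls; the early advantage rests on reading plotted pointwise intervals

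*Protocol article*

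**What the plan says.** The protocol article's Power analysis and sample size calculation section predicts that "GE individuals will demonstrate significantly larger brain volume (primary outcome measure) and stronger cognition scores (secondary outcome measures) prior to 20 YTO", with the reverse between 20 and 0 YTO. It states at least 90% power at p = .01 for every measure in Table 5 except cortical thickness.

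The section Statistical analysis using YTO Models sets out the analysis. An age and sex curve is fitted in GNE controls, and "The fitted values for this model are then subtracted from the dependent value to complete the correction". Then: "We assess the relationship between YTO and age- and sex-adjusted outcome measures in GE individuals using an additional mixed effects regression". The YTO terms are restricted cubic splines with degrees of freedom chosen by AIC. The inference rule takes the single p-value that this model gives for YTO. Of that p-value the article says: "which, if significant, indicates a statistically meaningful difference of GE from GNE along the YTO trajectory". The last step is graphical: "Finally, we plot these relationships and their 95% confidence intervals to determine where these differences occur along the trajectory".

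Two other places bear on this. Lessons from Kids-HD reports that "Striatal and pallidal volumes remain comparable in volume to GNE until 20 YTO after which they dramatically decline in volume". The Discussion says that reproducing the early-life advantages would "caution against mutant Huntington downregulation early in the disease process".

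**The concern.** The hypothesis is about level and sign on either side of 20 YTO. The p-value is about shape: whether corrected values change with YTO among GE participants. The tested model has no group term, and its intercept, which carries the overall level relative to GNE, is not part of the test. A process that only degenerates late, with no early benefit, can satisfy the test. A steady GE advantage at every YTO cannot.

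What remains for the early advantage is the plot. The article attaches to it no decision rule, no power and no mention that the subtracted GNE curve is itself an estimate. The stakes are not small, because the Discussion would draw a therapeutic caution from a replicated early advantage.

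**Working it through.** **1. The plan's own power figures.** Inputs from the power section and Table 5: 180 projected and 79 Kids-HD GE participants, the Kids-HD F values, ndf, ddf and alpha 0.01. Projected F = F × 180/79 = F × 2.278. NCP = (F − 2F/ddf − 1) × ndf, using projected F. Power = P(non-central chi-square > 99th percentile of chi-square on ndf).

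General Ability Index: 13.50 × 2.278 = 30.76 (stated 30.78); NCP = 30.76 − 2 × 30.76/87.66 − 1 = 29.06 (stated 29.445); power 0.998 (stated 0.997). Others, computed/stated: PANESS 0.957/0.956, cortical gray matter 0.995/0.995, thalamus 0.917/0.916, cortical thickness 0.407/0.406. All 15 rows reproduce, with NCPs within 3%. The arithmetic is sound.

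**2. What those F values test.** In Table 5 ndf runs from 1 to 5, matching the permitted spline degrees of freedom. Seven rows, including General Ability Index and cortical gray matter, have ndf = 1, which I read as a single YTO slope. Write the corrected GE value as a + b·YTO with b > 0. The F-test concerns b only. The mean difference from GNE is a + 35b over 50–20 YTO and a + 10b over 20–0 YTO. For the same b, and so the same expected F:
- a = −20b: crossover at 20 YTO, as hypothesised;
- a = −35b: no average early difference;
- a = −50b: GE at or below GNE throughout 50–0 YTO;
- a = 0: GE at or above GNE throughout.

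This needs no simulation assumption.

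**3. The document's own example.** Striatum and globus pallidus have the two largest Kids-HD F values in Table 5 (13.98 and 16.22), yet they are the structures described as comparable to GNE until 20 YTO.

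**4. Simulation with fixed 3-df splines.** 2,000 runs per scenario; 180 GE participants with 400 visits; 270 GNE participants with 630 visits (450 − 180 and 1,030 − 400). Assumed: baseline age uniform 6–30, CAG normal (44, SD 3) clipped to 40–60, between/within variances 0.8/0.2 treated as known, no family effect. Onset age was 21.54 + exp(9.556 − 0.146·CAG), which gives the article's worked example of 26 YTO (26.3 and 26.1).

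| True GE minus GNE | YTO test p < 0.05 | 95% interval at 35 YTO above zero |
|---|---|---|
| none | 7.0% | 3.5% |
| +0.5 SD at every YTO | 7.1% | 97.3% |
| zero until 20 YTO, then −0.08 SD per year | 95.7% | 3.6% |
| −0.3 SD until 20 YTO, then the same decline | 95.7% | 0% |
| crossover at 20 YTO | 91.8% | 92.1% |

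The p-value does not separate the last three rows. Carrying the GNE-fit variance widens the standard error at 35 YTO by about 13%; the interval rate then falls from 3.5% to 2.1% with no effect and from 92.1% to 88.2% under the crossover.

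**5. Simulation with AIC-chosen df, as the plan specifies.** 1,200 runs, assumed ICC 0.9, CAG 40–52 centred near 44. The YTO test rejects in 15.2% with no difference, 15.8% with a constant +0.4 SD, and 82.8% with degeneration only (zero until 20 YTO, then −0.06 SD per year). A joint 4-df test that includes the GE intercept rejects in 5.3%, 94.2% and 70.8%.

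Under degeneration only, the plotted interval lay above zero somewhere in 22.5–47.5 YTO in 26.5% of runs; a pre-set early contrast was falsely positive in 2.7%. Repeats at ICC 0.8 to 0.9 (500 to 700 runs per scenario) gave 72–88% for the YTO test and 13–27% for the scan. Looking only at 35 YTO gave 9–12%.

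**The case against.** The strongest defence is that the quoted inference is largely true. Outcomes are first corrected by the GNE curve, so if GE followed GNE exactly the corrected values would be flat at zero. A significant YTO effect therefore does imply a departure somewhere, and the article does not say that the p-value alone proves an early advantage. This stands.

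A reader might go further and infer that the plan cannot establish the early advantage at all. The documents do not support that. The fitted curve is a GE-minus-GNE estimate, and its interval against zero addresses level and sign. Under a constant +0.5 SD it lay above zero at 35 YTO in 97.3% of runs, and under the hypothesised crossover in 92.1%. Nor is it fair to predict that any significant p-value will be reported as an early benefit: the striatum and pallidum were reported as comparable to GNE until 20 YTO despite their large F values.

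It is also fair that a constant offset is not the stated hypothesis, that the article describes its power as power to reproduce the Kids-HD findings, and that contrasts or simultaneous bands may sit in an analysis plan not shown. But the article does not merely leave detail open. It fixes a test, powers it, and attaches an interpretation that omits what the test cannot show.

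**Conclusion.** The point holds in limited form and should be fixed. The YTO p-value establishes change across YTO among GE participants, and hence some departure from GNE, but not its sign or location. It is insensitive to a constant offset and readily significant under late degeneration alone. The early advantage then depends on a pointwise scan with no stated power or decision rule. Table 5 is correctly calculated, but it is power for change across YTO.

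The structural part follows from leaving the intercept out of the test and needs no simulation. The size of the scanning error, roughly a quarter against about 3%, depends on ICC, CAG distribution and effect shapes that the documents do not give, and on AIC selection of df; with fixed 3-df splines read at 35 YTO alone the rate was 3.6%. The raised null rejection rate (about 7% with fixed df, about 15% with AIC) is a related but separate matter and is not needed for this conclusion.

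**What to change.** In Statistical analysis using YTO Models, state that the YTO p-value shows variation across YTO only. Make the confirmatory tests two pre-set GE-minus-GNE contrasts, the mean difference over 50–20 YTO and over 20–0 YTO. Take both from one mixed model of both groups with a GE intercept and GE-specific YTO terms, so that uncertainty in the GNE curve is carried through. Claim an early advantage only if the first contrast is significantly above zero, and a crossover only if both are significant in the predicted directions. Because a crossover requires both, that claim needs no division of alpha between them. Keep the plots with 95% intervals as description.

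In Power analysis and sample size calculation, label Table 5 as power for change across YTO.

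The cost is wording and reanalysis code, with no new data. The drawback is that power for each contrast may be lower than the omnibus figure now quoted.

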To assess the relationship between age- and sex-adjusted neuroimaging variables (e.g., cortical grey and white matter volume, striatal volume, corticostriatal structural and functional connectivity, etc.) and clinical outcomes in GE individuals, we apply modeling techniques as described above. The models include random effects of subject and family, but exclude age and sex, as the values will have already been corrected using the data from GNE participants. Imaging measures are generally predictor variables, and clinical measures are the outcomes, reflecting the potential causal relationships between the two measurement classes. As in our previous work [17], we also split our GE participants into two groups with a cutoff of 20 YTO and test for differences in the imaging versus clinical relationships. This is based empirically on our work [17] showing divergence in neural and behavioral measures at this point in the YTO trajectory and because of work showing an upward trend in NfL at 20 YTO [18]. As described above, potential non-linear relationships between biomarkers and clinical measures are interrogated using restricted cubic splines (up to five degrees of freedom). For all analyses, a *p* value of < 0.05 is considered statistically significant.

In addition to our hypothesis-driven analyses, we also plan to perform detailed exploratory analyses to uncover novel neuroimaging biomarkers that both distinguish GE and GNE individuals and individuals with variations in HD-related single nucleotide polymorphisms (SNPs). For example, machine learning approaches, such as deep learning, have been applied to neuroimaging data from patients with neurodegenerative disorders to identify how those SNPs affect brain anatomy and function [81]. As mentioned above, SNPs in several genes explain variation in the eventual onset of motor symptoms in HD [32–34]. Using deep learning and other machine learning approaches as exploratory tools may reveal new mechanistic information about how these SNPs shape neurodevelopment and -degeneration.

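### The early GE advantage (50-20 YTO) is located by reading plotted 95% intervals after one overall YTO test, which a late decline alone can pass, so its error rate is not controlled

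*Protocol article*

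**What the plan says.** Under Statistical analysis using YTO Models, each outcome is first corrected for age and sex with a model fitted in gene-non-expanded (GNE) participants: "The fitted values for this model are then subtracted from the dependent value to complete the correction". Zero on the corrected scale therefore stands for GNE.

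The corrected values of GE participants are then regressed on YTO, with the curve "modeled using restricted cubic splines with degrees-of-freedom chosen by AIC". The GNE model, which the YTO model is said to resemble, allows up to five df, "with tied AIC values (≤ 1.0) favoring the simpler model". The p-value for YTO, "if significant, indicates a statistically meaningful difference of GE from GNE along the YTO trajectory". The last step is the plot: "we plot these relationships and their 95% confidence intervals to determine where these differences occur along the trajectory". The level for all analyses is a p "value of < 0.05 is considered statistically significant".

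The hypothesis that this serves is given under Power analysis and sample size calculation: "GE individuals will demonstrate significantly larger brain volume (primary outcome measure) and stronger cognition scores (secondary outcome measures) prior to 20 YTO", with the reverse between 20 and 0 YTO. No contrast for either region and no simultaneous band is stated. The split at 20 YTO in the same analysis section is for imaging-clinical relationships, not for the GE-GNE difference.

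**The concern.** The hypothesis is about sign and place: GE above GNE before 20 YTO, below it afterwards. The overall test asks only whether the curve varies with YTO anywhere. If GE participants merely decline after 20 YTO, the test is significant, and the 50-20 region is then searched with intervals that hold their 95% coverage at a single chosen YTO.

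The document itself reports this pattern. Lessons from Kids-HD says that striatal and pallidal volumes stayed comparable to GNE until 20 YTO and then fell sharply. The structural analysis section names the basal nuclei among the primary volume measures. For whole brain and cognition the earlier study did report an early advantage, so there a late decline alone is the alternative that a replication must be able to rule out.

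The stake is considerable. The Discussion says that reproducing the early advantage would support antagonistic pleiotropy and call for caution about lowering the mutant protein early. As planned, that statement has neither a controlled error rate nor a power figure.

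**Working it through.** **1. The plan's own figures.** Table 5 gives power for the overall YTO test at 0.01. Projected F = F × 180/79 = F × 2.278. NCP = (F − 2F/ddf − 1) × ndf, using the projected F and the tabulated ddf. Power comes from the non-central chi-square.
- General Ability Index: 13.50 × 2.278 = 30.76; NCP = 30.76 − 2 × 30.76/87.66 − 1 = 29.06; power 0.998 (table 0.997).
- Thalamus: 7.47 × 2.278 = 17.02; NCP 15.69; power 0.917 (table 0.916).
- Striatum: 13.98 × 2.278 = 31.85; NCP = (31.85 − 2 × 31.85/102.37 − 1) × 5 = 151.2; power >0.999 (table >0.999).

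The powers reproduce. They describe whether YTO matters at all, not whether an early advantage is shown. For striatum and globus pallidus, both >0.999, the overall test is almost certain to be passed if the earlier findings hold.

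**2. Simulation set-up.**
- From the document: 180 GE participants, about 400 visits (400/180 = 2.2 each; about 2.3 simulated), restricted cubic splines with 1-5 df, AIC with ties of 1.0 or less going to the simpler model, YTO test at 0.05.
- Assumed: YTO uniform on 3-50 or normal (mean 28, SD 10); intraclass correlation 0.6, 0.85 or 0.95; two knot placements; variance components known; no family effect.
- The true difference is zero from 50 to 20 YTO. After that there is either nothing or a linear or quadratic decline of the stated size at onset.
- Counted: YTO test significant and a pointwise 95% interval wholly above zero somewhere in 50-20 YTO.

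**3. False early GE advantage, %: mean (range over settings), GNE fit treated as known.**

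| True late decline | AIC-chosen df | Fixed 3 df | Fixed 5 df |
|---|---|---|---|
| None | 5.0 (3.9-6.4) | 2.3 (1.9-2.8) | 2.5 (2.0-3.2) |
| Linear 0.5 SD | 12.9 (9.6-15.9) | 6.6 (5.0-8.5) | 7.7 (5.5-11.0) |
| Linear 1 SD | 19.6 (15.9-24.0) | 9.4 (7.9-11.3) | 12.2 (9.9-14.1) |
| Linear 1.5 SD | 21.2 (16.4-25.3) | 10.8 (8.4-13.2) | 13.5 (10.4-15.5) |
| Linear 2.5 SD | 22.6 (15.1-29.1) | 12.5 (7.7-18.4) | 14.7 (11.7-17.1) |
| Quadratic 1 SD | 17.0 (11.2-23.0) | 10.6 (6.2-14.6) | 9.9 (6.0-13.9) |
| Quadratic 2 SD | 22.7 (18.6-27.6) | 20.2 (14.2-28.2) | 13.7 (10.9-15.5) |

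Adding the error of a GNE fit from 270 participants (450 − 180) raises the AIC figures for linear declines of 1-2.5 SD and the 2 SD quadratic decline to means of 23-26% (range 18-32%). A separate set of runs at intraclass correlation 0.6 or 0.85, with a 1-1.5 SD decline, gave 19-29% (AIC) and 9-17% (fixed 3 or 5 df), and 3-6% with no difference anywhere.

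**4. Where the excess comes from.** Simultaneous coverage over 50-0 YTO needs a multiplier of about 2.43, 2.70 or 2.83 for 1, 3 or 5 df. The bands widen by 2.43/1.96 = 1.24, 2.70/1.96 = 1.38 and 2.83/1.96 = 1.44. With such a band and the same late declines, the false early advantage falls to about 1-5% with fixed df in most settings. It reaches 9% for the worst-fitted shape (3 df, quadratic), or 16% with GNE error. With AIC-chosen df it stays at about 4-15%. So the search explains only part of the excess. In further runs with a 1-1.5 SD decline, a straight line forced through the data gave 21-69%, against 8-13% for a fixed 3-df curve.

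**5. The alternative.** One pre-specified contrast, the mean GE-GNE difference over 50-20 YTO from a fixed 3- or 5-df curve, gave 2.1-3.6%, close to the nominal 2.5% in one direction.

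**The case against.** A reader might infer that about one outcome in six will show a false early advantage whatever the truth, or that with no difference at all the intervals exclude zero in 16-38% of outcomes. The document does not support either reading. The 16-38% figures (16-17% for 1 df, 27-29% for 3, 36-38% for 5) ignore the YTO test that precedes the plot, and they count exclusions in either direction anywhere in 50-0 YTO. With the test in place and no true difference, a false early advantage appears in 4-6% (AIC) or 2-3% (fixed df). The text does not say in so many words that the plot is read only after a significant test; without that condition the figure is 9-17%.

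The word pointwise is also not in the document. This is an article, and a fuller plan could define the band. That limits the certainty, but pointwise is the ordinary meaning of a plotted 95% interval, and the rule that differences are located from the plot is stated.

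It is also fair to say that the search is not the only cause. AIC can pick a curve too stiff for a flat-then-falling shape, which pushes the early part above zero. That stands, and it means that wider bands alone would not cure the problem.

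**Conclusion.** The point holds in conditional form. The plan gives plotted intervals the task of deciding where GE differs from GNE, and the preceding test does not guard the 50-20 YTO region when the outcome truly declines late. For a decline of about 1 SD or more at onset and no early difference, a false early advantage is to be expected in roughly 15-30% of cases with AIC-chosen df, against a nominal 2.5%. With 3 or 5 df fixed in advance it is about 7-17% in most settings; a 3-df curve fitted to a strong quadratic decline does worse. For a weak linear decline (0.5 SD) the mean under AIC is about 13%.

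The direction of the result is secure. The exact rates are not, because the YTO distribution, the intraclass correlation and the size and shape of the decline are assumptions.

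**What to change.** In Statistical analysis using YTO Models, replace the sentence on plotted intervals with two rules.

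1. Test the hypothesis under Power analysis and sample size calculation with one pre-specified contrast per region: the mean GE-GNE difference over 50-20 YTO and over 20-0 YTO. Take both from a spline with pre-specified df, and state the weighting over YTO.
2. For any finer statement of where the groups differ, use a simultaneous 95% band over 50-0 YTO from that same spline, with the critical value simulated from the coefficient covariance or obtained by a participant or family bootstrap. Keep pointwise intervals as descriptive only.

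A simultaneous band placed on AIC-chosen df is not enough, as step 4 of the working shows. Both rules work better if the uncertainty of the GNE fit is carried into the standard errors.

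The cost is a few sentences and a few lines of code. The bands become about 25-45% wider, so the claimed regions will be shorter, and df fixed in advance give up some freedom to follow the data.
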